### 2.2. Trial Exclusion Criteria

A patient who is pregnant or breastfeeding.A patient who would not undergo a blood transfusion because of their religious beliefs.A patient who is participating in an intervention study for the treatment of COVID-19.A patient who has been vaccinated against SARS-CoV-2.A patient who has already undergone convalescent plasma transfusion.A patient with a history of allergy to a blood product.A patient with a deficiency in a plasma protein, such as IgA.A patient with New York Heart Association class III or IV heart failure.A patient whom the principal investigator, investigator, or sub-investigator judged to be ineligible for other reasons.

These exclusion criteria will help ensure the safety of study subjects, that the products used are acceptable to the study subjects, and that the evaluation of the efficacy of our planned intervention is not influenced by other SARS-CoV-2 treatments or vaccination.

### 2.3. Intervention

The intervention in this trial will be injectable COVID-19 convalescent plasma. This product will be the fresh frozen plasma collected by apheresis to remove most of the white blood cells. After being thawed, the liquid appears yellow to yellow-brown, sometimes cloudy because of lipids in the plasma. This product contains an anticoagulant solution (Acid Citrate Dextrose [ACD]-A solution) derived from apheresis. The collected plasma will be aliquoted in a volume of 100 mL; approximately 1.6 to 2.0 g (71 to 78 mEq) of sodium is present in 100 mL [20]. The neutralizing activity of purified IgG from convalescent plasma against SARS-CoV-2 will be evaluated using a previously described in vitro cell-based assay [18]. The neutralizing activity of convalescent plasma will be expressed as total neutralizing units (NU) by purified IgG neutralizing activity, the total amount of human IgG in the plasma, and the total volume of plasma [18]. The activity of the convalescent plasma will be classified into four stages (Supplementary Information S1).

Grade A: Potent neutralizing activity. The total neutralizing capacity of 200 mL of plasma is ≥18,000 NU (Supplementary Information S2).Grade B: Moderate neutralizing activity. The total neutralizing capacity of 200 mL of plasma is ≥9000 but <18,000 NU.Grade C: Mild neutralizing activity. The total neutralizing capacity of 200 mL of plasma is ≥4500 but <9000 NU.Grade X: Slight neutralizing activity. The total neutralizing capacity of 200 mL of plasma is <4500 NU.

In this trial, there are no required or restricted concomitant drugs or therapies, but other drugs are used as an investigational intervention for COVID-19.

### 2.4. Randomization and Blinding

Subjects will be randomized to the convalescent plasma group or the standard of care group at a ratio of 1:1 by the randomization system of the Electronic Data Capture (EDC) or a randomization system created separately from the EDC. The randomization program will be registered on the randomization system in advance. Detailed procedures for randomization will be specified separately in the procedure manual (outside the scope of review by the certified review board). The purpose of this trial is to evaluate whether convalescent plasma therapy should be added to usual care, and it will be difficult to conduct blind treatment, considering the invasiveness in regards to the subjects and effects on the standard of care. For clinical improvement as secondary endpoints, blinding could be made possible if independent persons assess it. However, many other parameters will be collected regardless of whether they are blinded or not, and unblinding is expected to have a negligible impact. Therefore, treatment will not be blinded in this trial.

Randomization will be stratified by the following factors:Age (≥60 or <60 years old).The number of days from the day of onset (set as day 0) until the scheduled day of convalescent plasma transfusion (≤3 or ≥4 d).Trial site.

### 2.5. Primary and Secondary Endpoints

The primary endpoint of the trial will be the time-weighted average changes in the SARS-CoV-2 virus load in nasopharyngeal swabs from day 0 to days 3 and 5. It is hypothesized that the intervention should result in a decrease in the viral load in the convalescent plasma group up to day 5. This endpoint (change in viral load) has been used as an index of therapeutic effect in several previous studies. 

The secondary endpoints are shown in Table 1.

### 2.6. Dosage and Administration

After consent is obtained from a subject, the convalescent plasma will be administered intravenously during the period between the day of onset (set as day 0) and day 5. It will be infused intravenously at 40 mL/h for the first 15 min after the start of infusion. If no adverse event is observed during the infusion, it will be continued at 100 mL/h. The infused volume will be dependent upon the following.

As one course of therapy, the infused volume of the plasma is 200 mL for Grade A, 400 mL for Grade B, and 800 mL for Grade C. When the volume of 800 mL is infused, it will be divided into 2 and 400 mL will be infused in a 24 h interval.

Plasma with blood types A, B, and O must be administered to the subjects with the same blood type. However, according to the Guidelines for the Use of Blood Products issued by the Ministry of Health, Labour and Welfare [20], plasma with blood type AB can be administered to subjects with blood types A, B, and O, unless there is plasma with the same blood type.

### 2.7. Treatment and Observation Periods (Including Follow-Up)

The Grade A and B convalescent plasma will be administered in a day, and the Grade C convalescent plasma will be administered in 2 d. The subjects will be observed according to the schedule shown in Table 2.

### 2.8. Observation and Test Parameters

Characteristics of each subject:
○Date of birth (age), sex, nationality/race, smoking history, complications, prior medical history, history of the current disease, and pregnancy status (premenopausal female subjects should undergo a pregnancy test).○Information on hospitalization (dates of admission and discharge).○Body height and weight.○Background data related to COVID-19 and overseas travel history.Physical findings:
○Status of supplemental oxygen and the use of mechanical ventilation.○Physical conditions will be examined by inspection, palpation, auscultation, and percussion.Vital signs:
○Level of consciousness○Body temperature (°C)○Blood pressure (mmHg)○Pulse rate (beats/min)○Respiratory rate (breaths/min)○SpO_2_ (%)Clinical condition:The clinical condition of each subject will be assessed according to the following:○Death○Hospitalization and the use of invasive mechanical ventilation or ECMO.○Hospitalization and the use of noninvasive mechanical ventilation or a high-flow oxygen device.○Hospitalization and supplemental oxygen requirement.○Not requiring hospitalization or supplemental oxygen but requiring the continuation of treatment (for COVID-19-related or other diseases).○Not requiring hospitalization, supplemental oxygen, or the continuation of treatment.○Not requiring hospitalization, but requiring the limitation of activities and/or oxygen therapy at home.○Not requiring hospitalization or the limitation of activities.Laboratory tests (Table 3)ImagingPlain chest X-ray

The appropriateness of the incorporated participants and the data collected were monitored on a regular basis to ensure quality.

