## Figures and Tables

**Table 1 life-12-00856-t001:** Secondary endpoints of the trial.

Objective	Endpoint	Rationale for the Endpoint
Prevention of mechanical ventilation or death.	Use of mechanical ventilation or death by days 14 and 28.	Prognosis is an endpoint that is not subjective.
Prevention of death.	Mortality on days 14 and 28.	Prognosis is an endpoint that is not subjective.
Prevention of the need for supplemental oxygen use.	Percentage of subjects who used oxygen on days 3, 5, 7, 14, and 28.	It is an endpoint that is not subjective.
To assess the shortening of the duration of symptoms (the time to clinical improvement).	Clinical improvement is defined as the first day a subject meets one of the three categories on the ordinal scale shown below: Not requiring hospitalization or supplemental oxygen and not requiring continuation of treatment. No hospitalization is needed but requires the limitation of activities and/or oxygen therapy at home. No hospitalization and no limitation of activities.	Clinical improvement is related to efficacy.
To assess clinical improvement on days 3, 5, 7, 14, and 28 in subjects given the convalescent plasma.	Clinical improvement on days 3, 5, 7, 14, and 28 (on an 8-point scale)	Clinical improvement is related to efficacy.
Time to improvement on the National Early Warning Score, UK (NEWS)	Time to discharge from the hospital or the maintenance of NEWS ≤2 for 24 h (whichever occurs first) NEWS on days 3, 5, 7, 14, and 28.	Clinical improvement is related to efficacy.
Decrease in the viral load in the convalescent plasma group after convalescent plasma transfusion.	Time-weighted average change and the numerical change in the SARS-CoV-2 virus load in nasopharyngeal swabs from day 0 to each day of assessment.	Change in the viral load has been used as the index of the therapeutic effect in many studies.
To assess safety after convalescent plasma transfusion.	Occurrence of adverse events.	It is necessary to evaluate safety.
To screen and identify variants.	Determine if variants are present in nasopharyngeal swab samples on day 0	Variants are related to efficacy because it has been reported that variants may reduce the antiviral activity of neutralizing antibodies.

**Table 2 life-12-00856-t002:** Study schedule.

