Activities	Admission		Day 0 (Day of Transfusion) ^i^		Day 1 (1 d after Transfusion)	Day 3 (3 d after Transfusion)	Day 5 (5 d after Transfusion)	Day 7 (7 d after Transfusion)	Day 14 (14 d after Transfusion)	Day 21 (21 d after Transfusion)	Day 28 (28 d after Transfusion)	Day 90 (90 d after Transfusion)	Discontinuation of the Study
			Before Trans- Fusion	3 h after Start of Trans-Fusion ^j^									
Acceptable time window ^a^	−3 to 0		Reference day		+1	±1	±1	±1	±3	±3	±3	+30	–
Informed consent	X												
Confirmation of eligibility		X ^k^											
Registration and randomization of a subject		X											
Characteristics of a subject		X ^k^											
Plasma transfusion ^h^			X		X ^b^								
Vital signs ^d^ and clinical condition ^c^			X	X ^h^	Once daily during hospitalization and days 3, 5, 7, 14, 21, and 28 after discharge								X
Physical findings ^d^		X ^k^	X	X ^h^	X	X	X	X	X	X	X		X
Pregnancy test ^l^		X ^k^											
Collection of swabs (2 sticks) ^m^			X		X	X	X	X	X	X	X		X ^e^
Blood test (biochemistry, complete blood count, and coagulation) ^m^		X ^k^			X	X	X	X	X	X	X		
Blood test (blood type)		X ^k^											
Blood test (cross-match) ^h^		X											
Blood test (infection screening) ^f^		X ^k^											
Blood test (post-transfusion infection test) ^g,h^												X	
Storage of plasma ^m^			X		X	X	X	X	X	X	X		
Storage of serum ^m^			X		X	X	X	X	X	X	X		
Radiography (chest X-ray)		X ^k^											
Concomitant drugs ^c^			X		Every day during hospitalization and days 3, 5, 7, 14, 21, and 28 after discharge								X
Adverse events ^c^				X ^h^	Every day during hospitalization and days 3, 5, 7, 14, 21, and 28 after discharge							X ^h^	X

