^a^ If the days overlap because of the acceptable time window, it is not allowed to collect the data for 2 d on the same day (e.g., it is not allowed to collect the data for both day 1 and day 3 on day 2). ^b^ When Grade C plasma is used, it will be infused on day 1. ^c^ When a subject has been discharged, the data can be collected by phone on or after day 7. ^d^ When a subject has been discharged, it is allowed to not collect data on or after day 7. ^e^ This should be performed if a subject discontinues the study on and before day 14. ^f^ Similar to tests for infectious diseases conducted at registration, HBsAg, HBsAb, HCVAb, HIV-1/2Ab, Syphilis-RPR/TPHA, and HTLV-1 Ab should be measured. ^g^ Similar to the post-transfusion infection test, HBV-DNA quantification, HCV core protein, and HIV-1/2Ab assays should be performed (the test should also be performed in a subject who has stopped transfusion prematurely). ^h^ These data will be collected in the convalescent plasma group. ^i^ The date of transfusion scheduled at the time of randomization is day 0 in both the convalescent plasma group and the standard of care group. ^j^ When Grade C plasma is used, the data to be collected 3 h after the start of transfusion on day 0 should be collected both on days of first and second transfusions. ^k^ The results of the tests as the regular practice before informed consent can be used. ^l^ It is performed in premenopausal female subjects. ^m^ When a subject has been discharged, it is allowed to not collect samples on or after day 14.

**Table 3 life-12-00856-t003:** Laboratory tests performed as part of the trial.

Hematology	Hemoglobin, Hematocrit, White Blood Cell Count with Differential, and Platelet Count
Coagulation	APTT, PT-INR, and D-Dimer
Blood biochemistry	Albumin, AST, ALT, bilirubin, CRP, blood glucose, urea nitrogen, creatinine, LDH, creatine kinase, potassium, and sodium
Infection screening	HBsAg, HBsAb, HCVAb, HIV-1/2Ab, Syphilis-RPR/TPHA, and HTLV-1Ab.
Pregnancy test	Urine or blood (HCG)
Blood type and cross-match	Blood type: A/O/B/AB, Rh +/−; cross-match: compatible/incompatible
SARS-CoV-2 viral load	Nasopharyngeal swabs
Samples for storage	Serum (1.5 mL) and plasma (1.5 mL)
Post-transfusion infection test	HBV-DNA quantification, HCV core protein, and HIV-1/2Ab

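### Oxygen use on days 7, 14 and 28 is undetermined for discharged subjects in the merged home-oxygen level of the clinical scale whose physical findings were skipped

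*Protocol article*

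**What the plan says.** Four places in the protocol article bear on this.

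- **Where the item sits.** Section 2.8 opens its list of physical findings with "Status of supplemental oxygen and the use of mechanical ventilation".
- **When it may be skipped.** In Table 2 the physical-findings row carries footnote d: "When a subject has been discharged, it is allowed to not collect data on or after day 7".
- **What the endpoint needs.** Table 1 defines the oxygen endpoint as "Percentage of subjects who used oxygen on days 3, 5, 7, 14, and 28".
- **What is still collected.** The Table 2 row "Vital signs ^d^ and clinical condition ^c" gives the two items different footnotes. Clinical condition is scheduled "Once daily during hospitalization and days 3, 5, 7, 14, 21, and 28 after discharge". Its footnote c reads "When a subject has been discharged, the data can be collected by phone on or after day 7", which allows a phone call but not omission. One of the eight levels of this scale in section 2.8 is "Not requiring hospitalization, but requiring the limitation of activities and/or oxygen therapy at home".

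**The concern.** Three of the five time points of the oxygen endpoint (days 7, 14 and 28) fall in the period when the only item that records oxygen status directly is optional for discharged subjects. The remaining source is the clinical-condition scale. Its one level that mentions oxygen at home does not separate a subject on oxygen from a subject who is merely limited in activity.

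A status that was never collected cannot be restored at analysis. Table 1 justifies this endpoint as one that is not subjective, and that reasoning weakens if oxygen use must be guessed from a level shared with activity limitation. The trial is open-label, so the timing of discharge could differ between arms, and the number of unknowns with it.

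**Working it through.** No figure in the article depends on this point, so there is none to reproduce. The check maps each scale level to oxygen use and then sizes the remainder under stated assumptions.

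**Step 1. What each level says about oxygen** (order as printed in section 2.8)

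| Level | Oxygen use |
|---|---|
| 1. Death | no current status |
| 2. In hospital, invasive ventilation or ECMO | yes |
| 3. In hospital, noninvasive ventilation or high-flow oxygen | yes |
| 4. In hospital, supplemental oxygen | yes |
| 5. Out of hospital, no oxygen, treatment continuing | no, as stated |
| 6. Out of hospital, no oxygen, no continuing treatment | no, as stated |
| 7. Out of hospital, activity limitation and/or home oxygen | **unknown** |
| 8. Out of hospital, no activity limitation | no, by implication, since home oxygen belongs to level 7 |

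Of the four levels printed as out of hospital, three can be scored and one cannot.

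**Step 2. Who is left undetermined.** A subject must meet all of these conditions: discharged; assessed on day 7, 14 or 28; at level 7; and physical findings not collected. Days 3 and 5 are unaffected, because footnote d starts at day 7.

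**Step 3. Size.** Inputs:

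- From the article: 200 patients (section 2.12) at 1:1 (section 2.4), so 100 per arm.
- Assumed, because the article gives none of these: 60 discharged in one arm and 70 in the other; 5 true oxygen users per arm, none of them at level 7; 5% to 30% of discharged subjects at level 7, all with physical findings skipped.

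Unknown per arm = discharged × share at level 7. Percentage if the unknowns are excluded = 5 / (100 − unknown). Highest possible percentage if every unknown were on oxygen = (5 + unknown) / 100.

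| Discharged | Share at level 7 | Unknown | Excluding unknowns | Highest possible |
|---|---|---|---|---|
| 60 | 5% | 3 | 5/97 = 5.15% | 8% |
| 70 | 5% | 3.5 | 5/96.5 = 5.18% | 8.5% |
| 60 | 30% | 18 | 5/82 = 6.10% | 23% |
| 70 | 30% | 21 | 5/79 = 6.33% | 26% |

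With no true difference between arms, excluding the unknowns creates a gap of 5.18 − 5.15 = 0.03 points at the 5% share and 6.33 − 6.10 = 0.23 points at the 30% share. The inflation of a true 5% is 100/97 = 1.03-fold to 100/79 = 1.27-fold.

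**The case against.** The strongest reply is that the scale already does most of the work. Clinical condition is required after discharge and classifies everyone outside level 7. Footnote d permits skipping and does not demand it. The article condenses a longer protocol, and the case report form, which may already ask about oxygen by phone, is not shown. Denominators and missing-data rules belong to the analysis plan in Supplementary Information S4, also not shown.

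Most of this stands, and it rules out three stronger readings that a reader might infer.

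- **That the endpoint cannot be scored for any discharged subject.** The scale scores levels 5, 6 and 8 as no oxygen. Levels 5 and 6 are oddly placed: no printed level covers an inpatient without oxygen, and sites may in practice use these two for such patients. That is an inference. Even then level 8 is scorable and level 7 remains the only gap.
- **That the percentage would be taken among those still in hospital.** With the assumptions above, that would give 5/40 = 12.5% against 5/30 = 16.7%. It drops every discharged subject, including those whom the scale scores as off oxygen, and nothing in Table 1 restricts the denominator in this way.
- **That the ventilation-or-death endpoint is lost as well.** Both ventilation levels are in-hospital levels, and clinical condition is recorded daily during hospitalization, with no limit to the first stay. Footnote d does not reach that endpoint on its natural reading. SpO2 is not an input to the oxygen-use endpoint either.

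What the reply does not remove is the conflict in the article itself: a named endpoint needs an item on days when a stated rule makes that item optional, and the fallback is ambiguous at one level. An analysis plan can say how to handle the unknowns but cannot recover their status.

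**Conclusion.** The point holds in a narrow form. Oxygen use on days 7, 14 and 28 is undetermined for discharged subjects at the merged level whose physical findings were not collected. Under the assumptions shown, that is about 3 to 21 subjects per arm. Excluding them would move a true 5% to about 5.2% to 6.3%, so the likely bias is small. The uncertainty is wider than the bias: at the upper end the unknowns outnumber the 5 assumed users, and the true percentage could lie anywhere between 5% and 26%.

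The discharge rates, the number of oxygen users and the share at the merged level are all assumptions. If sites record the item despite footnote d, or the form already asks for it by phone, the gap shrinks or closes. This is a minor point on one secondary endpoint. The primary endpoint is untouched.

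**What to change.** Move the oxygen and ventilation status item out of footnote d and place it under footnote c, so that it may be taken by phone but not omitted. At the contacts already scheduled on days 7, 14 and 28, record one item: on supplemental oxygen today, at home or in hospital, yes or no. Score the oxygen endpoint from that item and not from the merged scale level, with all randomised subjects in the denominator. The eight-level scale can stay as it is for its own endpoints.

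The cost is a change of footnote, one yes/no field and slightly longer phone calls. If the full protocol or the case report form already contains such an item, it is enough to correct the footnote and name the item as the source of the endpoint.

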### 2.1. Trial Inclusion Criteria

A patient who, or whose legal representative, has provided written consent for the participation of the patient in the trial.A hospitalized patient with a confirmed diagnosis of COVID-19 based on a reverse transcription-PCR (RT-PCR) or loop-mediated isothermal amplification (LAMP) assay, antigen test, or other means.A patient who met all of the following criteria upon admission to a hospital:
○Patients who can begin receiving study treatment within 5 d after onset.○Patients with SpO_2_ ≥ 95% on room air.○Patients aged ≥ 40 years or having at least one of the following underlying diseases: renal impairment, chronic obstructive pulmonary disease, cardiovascular disease, cerebrovascular disorder, malignant tumor, obesity, diabetes mellitus, hypertension, and an immunosuppressive state.A patient aged at least 20 years at the time of informed consent.A patient who has been infected with SARS-CoV-2 for the first time.Our inclusion criteria have been chosen to ensure that the patients are appropriately and ethically included in our study, have a milder form of the disease, are in the appropriate age group, and do not already have SARS-CoV-2 antibodies at the point of enrollment.

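### The printed 8-point clinical scale has no level for a patient in hospital without oxygen, and levels 5–6 overlap levels 7–8, so the scale scores on the assessment days are not uniquely defined

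*Protocol article*

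**What the plan says.** Section 2.8 of the protocol article lists eight clinical conditions without numbering them. They are numbered here in printed order, from 1 (death) to 8.

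- **Levels that state hospitalisation.** Level 2 is "Hospitalization and the use of invasive mechanical ventilation or ECMO", level 3 is "Hospitalization and the use of noninvasive mechanical ventilation or a high-flow oxygen device" and level 4 is "Hospitalization and supplemental oxygen requirement".
- **Levels that exclude a need for hospital care.** Level 5 is "Not requiring hospitalization or supplemental oxygen but requiring the continuation of treatment (for COVID-19-related or other diseases" and level 6 is "Not requiring hospitalization, supplemental oxygen, or the continuation of treatment". Level 7 is limited activity, oxygen at home, or both. Level 8 is no limitation of activity.
- **Entry state.** Section 2.1 requires "A hospitalized patient with a confirmed diagnosis of COVID-19" and, on admission, "Patients with SpO_2_ ≥ 95% on room air".
- **Endpoints.** Table 1 uses the scale twice. Time to clinical improvement runs to the first day in any of three categories, which correspond to levels 6, 7 and 8; the middle one reads "No hospitalization is needed but requires the limitation of activities and/or oxygen therapy at home". Level 5 is not among them, and Table 1's wording of level 6 again excludes a need for hospital care. A separate endpoint uses the 8-point scale on days 3, 5, 7, 14 and 28.
- **Assessment.** Table 2 has clinical condition recorded before transfusion on day 0, daily in hospital, and on set days after discharge. Section 2.4 notes that independent assessors could make clinical improvement a blinded assessment, but leaves the trial unblinded.

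**The concern.** An ordinal scale can be analysed only if every patient on every assessment day belongs to exactly one level. Here the state in which the trial recruits, in hospital and off oxygen, appears to have no level, while a discharged patient off oxygen appears to have two.

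Two secondary efficacy endpoints depend on the scale. If the levels are neither exhaustive nor exclusive, the score depends on a choice the article does not settle, made by an assessor who knows the treatment. The sharpest case is level 5 against levels 7 and 8, because level 5 is not an improvement and the other two are.

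**Working it through.** No arithmetic figure in the plan is at issue. The check is an enumeration of the printed wording.

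**Inputs.** The seven living levels in section 2.8, and the improvement categories in Table 1 (levels 6, 7 and 8).

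**Method.** Each living state is described by place (in or out of hospital), oxygen support, treatment continuing or not, and activity limited or not. In hospital there are 4 kinds of support (none, oxygen, noninvasive or high-flow, invasive), giving 4 × 2 × 2 = 16 states. Out of hospital there are 2 (none, home oxygen), giving 2 × 2 × 2 = 8 states. The total is 24. High-flow oxygen is coded as level 3 only.

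| Place | Oxygen | Treatment | Activity | Matching levels | Improvement? |
|---|---|---|---|---|---|
| In hospital | none | any | any | none (4 states) | not stated |
| In hospital | oxygen | any | any | 4 (4 states) | no |
| In hospital | noninvasive or high-flow | any | any | 3 (4 states) | no |
| In hospital | invasive | any | any | 2 (4 states) | no |
| Out | none | continuing | limited | 5 and 7 | no / yes |
| Out | none | continuing | not limited | 5 and 8 | no / yes |
| Out | none | ended | limited | 6 and 7 | yes |
| Out | none | ended | not limited | 6 and 8 | yes |
| Out | home oxygen | any | limited | 7 (2 states) | yes |
| Out | home oxygen | any | not limited | 7 and 8 (2 states) | yes |

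**Count.** No level: 4 states. Exactly one level: 12 + 2 = 14. Two levels: 4 + 2 = 6. Check: 4 + 14 + 6 = 24. Of the 8 out-of-hospital states, 6 match two levels, and in 2 of those 6 one level is an improvement and the other is not. These are counts of states, not of patients.

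**Scale on days 3, 5, 7, 14 and 28.** A patient still in hospital off oxygen on one of these days has no valid score. A patient out of hospital and off oxygen has two.

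**Time to clinical improvement.** Table 1 asks whether any of the three categories is met. A patient who does not need hospital care either has limited activity (level 7) or does not (level 8), so always meets one. Three consequences follow:

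1. Read literally, the event is the first day without a need for hospital care, and level 5 can never act as a non-event level.
2. If one level is recorded per day, the 5/7 and 5/8 states can be scored either way and the event date moves with the choice.
3. A patient still in hospital, off oxygen and no longer needing treatment fits no printed level, so it is unclear whether that patient has improved.

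**Alternative reading.** Not requiring hospitalisation could mean being in hospital without medical need. A patient who needs hospital care but not oxygen would still have no level, and levels 5 and 6 would still overlap 7 and 8.

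**Check of a repair.** Suppose levels 5 and 6 are worded as in hospital without supplemental oxygen, with and without continuing treatment. The 4 states with no level then have one each, and the 4 out-of-hospital, no-oxygen states fall to one each. The 2 states with home oxygen and unlimited activity still match both 7 and 8, so the boundary between those two levels also needs a word.

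**The case against.** The strongest reply has several parts.

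- **A wording slip in a condensed article.** The home appears first in level 7, and levels 5 and 6 sit between the in-hospital oxygen levels and the home levels. That order makes sense if 5 and 6 were meant for inpatients, and the full protocol (version 2.4) is not shown. This is plausible, but the scale is printed in full, neither section 2.8 nor Table 1 gives that meaning, and Table 1 repeats the wording. What sites were told in forms or manuals cannot be judged from the article.
- **Time to improvement is defined.** A reader might infer that this endpoint has no unique date at all. Table 1's any-of wording does give a date for most states, and overlap among levels 6, 7 and 8 cannot move it because all three are improvements. This part stands. What remains is the conflict of level 5 with 7 or 8 under single-level recording, and the in-hospital state off oxygen and off treatment.
- **Day 0 is not an endpoint day.** A reader might infer that the gap spoils the result of nearly every patient because nearly all start in the missing state. The score is recorded on day 0, but neither endpoint uses it. The gap matters for patients still in hospital off oxygen on a scoring day.
- **Home oxygen as improvement.** A reader might infer an error because patients enter on room air. It is a stated definition, not a contradiction, and Table 1 reports oxygen use separately on the same days. The same holds for defining improvement without reference to the day-0 level. Neither is pressed here.

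**Conclusion.** The point holds as a moderate defect in the wording of section 2.8 and Table 1. The scale is neither exhaustive (4 of 24 living states have no level) nor exclusive (6 of 24 have two). The day-by-day scale endpoint is the one mainly affected. Time to clinical improvement is affected only in the specific cases set out above.

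The number of patients affected cannot be derived, because the article gives no figure for how many remain in hospital off oxygen on each scoring day or continue treatment after discharge. That most discharged patients have two scores assumes that most leave without home oxygen. Level 5 covers treatment for other diseases as well, and section 2.1 admits patients with chronic conditions, so the 5/7 and 5/8 states should not be assumed rare.

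A reader might infer that this must be settled before the trial can be interpreted at all. The documents do not support that: the primary endpoint is viral load, and the mortality, ventilation and oxygen-use endpoints do not use this scale.

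**What to change.** Reconcile section 2.8 and Table 1 so that each state has exactly one level. One way is to word levels 5 and 6 as in hospital without supplemental oxygen, with and without continuing treatment, to match Table 1's first improvement category to the new level 6, and to state which of levels 7 and 8 takes a patient on home oxygen with unlimited activity. Under this wording, being in hospital off oxygen and off treatment would count as improvement, and so would being out of hospital with treatment continuing. The sponsor should confirm that both are intended.

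Section 2.10 schedules the observation period to end on 31 March 2022. If data are already collected, fix a written derivation rule before analysis and report it with the results.

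The cost is small: wording and a rule. Past scores may not be fully recoverable. Section 2.8 lists oxygen status under physical findings, which Table 2 schedules by visit rather than daily and allows to be skipped after discharge from day 7. Activity limitation is listed only within the scale itself. Where a score cannot be rebuilt, report how many are affected.
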